The aim of phase 1 is to evaluate the design elements of the virtual shopping environment to identify any factors that may hinder the ability of participants to effectively perform tasks in the virtual environment, identify the risk of physical distress, and obtain user feedback about realism and functionality. The primary hypothesis for the UX study is that the VR environment will be acceptable; however, some users will exhibit minor difficulties using the controllers and interacting with the environment. The primary outcome measures will be observational ratings assessing user difficulties with controller use, interacting with objects, and moving in the environment. The secondary hypotheses include that participants will report only minimal feelings of distress, will report that the virtual grocery store appears realistic and immersive, and will provide a general positive response to the experience with additional helpful ideas about how the experience could be improved.

The primary aim of phase 2 is to evaluate individual and environmental characteristics associated with susceptibility to experiencing CF in the context of performing an IADL, specifically shopping. Our primary hypothesis in phase 2 is that individuals performing structured grocery tasks will report more CF than simple exploratory behavior in the grocery store and that individuals experiencing distractions and interruptions will report more fatigue than those who do not experience interruptions. The primary outcome measure in phase 2 is the self-reported change by participants in CF by shopping experience. The secondary aims of phase 2 are to identify performance and eye-tracking measures that objectively identify fatigue, cognitive abilities, personality characteristics, shopping experience, or transient mood states that affect susceptibility to fatigue during shopping. Specific secondary exploratory hypotheses include that perceived workload increases with time on task for structured tasks and disruptive environments, percent eye closure and gaze shift increase with time on task and are associated with self-reported fatigue, and shopping accuracy declines with time on task.

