### Shopping Training

The participant will appear in a small version of the grocery store. They will be instructed on how to use the virtual cell phone to check their shopping list, review items in their cart, and answer text messages with the left-hand controller. They will be instructed on how to teleport and select items off the shelf with the right-hand controller. In the shopping training task, the participant must follow specific directions and must correctly put four items in their cart from the shopping list, one of which must be returned to the shelf, and they must answer a text to complete the shopping training. To complete the shopping portion of the task, the participant will need to teleport successfully to multiple shelves and aisles.

### Shopping Experience Number 1

Experience number 1 will be a control experience that will allow the participant to explore the grocery store with no specific task to complete. The shopping environment includes a few avatars and some low music in the background to simulate a realistic shopping environment during off-hours. All shopping actions will be enabled, and the participant may select items and place them in the shopping cart. The only requirement will be that they remain in the environment for 30 minutes. The control experience will evaluate whether the VR environment itself induces significant fatigue that may confound the interpretation of task-specific fatigue induction.

### Shopping Experience Number 2

Experience number 2 is a standard shopping experience designed to mimic a realistic shopping experience during a typical day. Participants will be provided with a shopping scenario. They will be told that they are shopping for sick friends. The participant will try to obtain as many items as possible from the cell phone shopping list. Participants will traverse the grocery store to find objects on the list and place them in the shopping cart. Avatars are present in the store but do not hinder progress or create any specific distractions. The background sound includes typical background noise, music, and overhead announcements. This condition assesses the cognitive load and fatigue related to the mental activity of shopping.

### Shopping Experience Number 3

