### Participants

The participants will be recruited from a local metro region. We anticipate that participant background characteristics (eg, education, ethnicity, sex, and age) will be representative of the metro area in background characteristics (eg, education, ethnicity, sex, and age). Recruitment will be managed by the National Institutes of Health (NIH) Office of Patient Recruitment, using local flyers; Office of Patient Recruitment website; and posts on social media, including Facebook and Twitter. Participants will be remunerated to participate in the study. All protocol activities will take place in a local NIH facility in Bethesda, Maryland. 

For each phase of the study, participants will be healthy individuals aged 18-75 years. Recruitment for phase 1 will target an older (≥55 years) and younger group (18-54 years) with 50% targeted for each group, stratified by sex. Recruiting a broad age range will ensure usability among older individuals, as future apps will likely involve older adult clinical populations. The sample will be stratified by sex, as some research suggests that women may experience immersive VR differently from men [116,117]. The phase 1 sample size will be 24, with 8 participants completing each of the three shopping conditions. Evaluating participants from a variety of backgrounds is important in UX research to identify any systematic issues in the interface, content, or instructions. The phase 2 study recruited 60 healthy individuals aged 18-75 years. For this study, there will be no targeted recruitment of older adults, as any design issues specifically associated with subject age will be addressed before phase 2. The sample size was determined based on the calculated effect sizes of fatigue induction studies that used the VAS-F (Cohen *d*=0.65; SD 0.25) and vigilance decrement studies [34]. The inclusion and exclusion criteria are included in Textbox 1.

Inclusion and exclusion criteria.

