For example, we will use the repeated measures ANOVA to test the primary hypothesis that the cognitive activity of shopping for specific items will create a greater perception of mental workload and fatigue compared with just exploring the environment unless the distribution of dependent measures does not allow for using this specific statistical procedure. Similarly, we will use an appropriate correlation procedure to compare the level of activity measures such as distance traversed in the store, number of items selected and reviewed, and efficiency and accuracy of shopping activity with perceptions of fatigue and workload. Correlation procedures will be used to assess the relationships between constructs, such as personality style, cognitive ability, fatigue susceptibility with self-reported mental workload, and fatigue to identify individual differences in fatigue susceptibility. Eye tracking such as percent eye closure will be explored as a possible objective indicator of fatigue by serving as a dependent measure in the repeated measures ANOVA by shopping experience and in correlational analysis with self-reported fatigue and workload. The actual analysis considers the appropriateness for each specific variable distribution.

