### Strengths and Limitations of This Study

CF is a complex phenomenon influenced by task, environment, personal experience, and individual differences. Our experimental conditions included a familiar task performed in a realistic immersive VR environment that allows for the precise control of stimuli. The ability to control stimuli and timing of events will enable us to determine the relative contribution of distraction, boredom, task complexity, and person characteristics on the development of CF. The strength of the immersive VR experience is the capacity to create a cognitive experience that closely aligns with real-life demands. Our ability to control the presence and timing of interfering factors enables us to assess environmental influences that would be almost impossible to standardize using an actual grocery store.

The immersive VR environment allows us to seamlessly use multiple measures of CF. We will use subjective indicators of CF and workload to better understand how perceived fatigue (eg, physical fatigue: *tiredness* and *sleepiness;* cognitive fatigue: *efficiency* and *difficulty in concentrating*) and workload (eg, mental demand, effort, and frustration) relate to the effects of tasks, environments, and other factors. Potential objective measures of CF, such as changes in behavior (eg, performance efficiency, shopping list rechecking, rate, and the efficiency of movement) and changes in eye movement, can be measured unobtrusively. The use of a randomized controlled design is a strength of this study. Participants will be randomly assigned to 1 of the 3 shopping conditions to control for any confounding effects of person-level background characteristics (eg, age) that may affect fatigue or reactions to the VR experience.

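### The phase 2 trait correlations have no trait-by-condition contrast, so they cannot show susceptibility to fatigue that is specific to shopping

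*Protocol article*

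**What the plan says.** Under Objectives, the primary aim of phase 2 covers individual and environmental characteristics associated with "susceptibility to experiencing CF in the context of performing an IADL, specifically shopping". The secondary aims again tie traits and mood states to fatigue while shopping.

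Under Shopping Experience Number 1, the control arm explores the store with no assigned task, and "The only requirement will be that they remain in the environment for 30 minutes". Its stated purpose is to evaluate whether the "VR environment itself induces significant fatigue that may confound the interpretation of task-specific fatigue induction". Strengths and Limitations names VR-induced eye strain and fatigue as the study's main weakness.

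Under Analysis, Phase 2, the ANOVAs are specified by shopping experience. The trait analyses are a third series, done primarily by correlation. Traits, mood and cognitive scores are related to fatigue and workload, ending with "fatigue susceptibility with self-reported mental workload, and fatigue to identify individual differences in fatigue susceptibility". For these correlations the text names no analysis set, stratification, adjustment for condition or trait-by-condition term.

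On numbers, "The phase 2 study recruited 60 healthy individuals aged 18-75 years", and "Participants will be randomly assigned to 1 of the 3 shopping conditions". The phase 2 allocation ratio is not given.

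**The concern.** The protocol identifies a rival explanation for fatigue, namely time in the headset, and builds an arm to isolate it. That arm is used for the comparison of means but not for the trait question. Yet the question of who is susceptible when shopping needs the control just as much. A trait that predicts tiring after 30 minutes in any VR session will correlate with fatigue whether or not anyone shops. To call it shopping-specific, its slope must be larger in shoppers than in explorers. A single correlation coefficient holds no information on that difference.

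At stake is the individual-characteristics half of the stated primary aim. The protocol intends later studies in clinical populations, and those could carry forward traits that mark tolerance of VR and not susceptibility to a daily activity. A second, conditional cost is dilution: if explorers are pooled with shoppers, a trait that acts only during assigned shopping is estimated with a weakened correlation.

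**Working it through.** **The plan's own figure.** The sample size of 60 rests on "Cohen *d*=0.65; SD 0.25", with no alpha, power or test stated, so it cannot be reproduced as written. At two-sided alpha 0.05 (assumed), a paired pre/post test at d=0.65 needs 21 per arm for 80% power, and 20 per arm gives 78.7%. A comparison of two arms needs 38 per arm, and 20 per arm gives 54%. No figure is given for the trait correlations, and nothing below depends on d=0.65 except one set of assumed arm means.

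**Assumptions.** 20 per arm; normal linear model; standardised trait T; residual SD 1; two-sided alpha 0.05; arm means in SD units of (0, 0, 0), (0, 0.65, 0.65) or (0, 0.65, 1.3); the same trait slope in experiences 2 and 3. A within-arm correlation r corresponds to slope b = r/√(1−r²). For r=0.4, b = 0.4/√0.84 = 0.436 and b² = 0.190.

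**1. Trait acts equally in every arm (headset or time effect only), r=0.4.** Share of trials significant, 3,000 simulated trials per scenario:

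| Analysis | Share significant |
|---|---|
| Correlation, all 60 | 82–90% |
| Correlation, 40 shoppers only | 70–75% |
| Trait × (experience 2 or 3 versus 1) | about 5% |

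The ranges span the three sets of arm means. Leaving out the control barely changes the result; only the slope contrast holds its nominal level.

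**2. Trait acts only in shoppers, r=0.4, control pooled.**
- Covariance = (2/3) × 0.436 = 0.291.
- Equal arm means: variance = 1 + (2/3) × 0.190 = 1.127, so r = 0.291/√1.127 = 0.27.
- Arm means 0, 0.65, 1.3: between-arm variance = 2 × 0.65²/3 = 0.282, so r = 0.291/√1.409 = 0.25.
- Power by Fisher z = Φ(atanh(r)·√(n−3) − 1.96). For r=0.274, n=60: Φ(0.281 × 7.55 − 1.96) = 57%. For r=0.245: 47%.
- Shoppers only, n=40: r = 0.38–0.40, power 69–73%. At r=0.40: Φ(0.424 × 6.08 − 1.96) = 73%.

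Over r = 0.30 to 0.50, pooled r runs from 0.18–0.20 (28–34% power) to 0.31–0.35 (69–78%). In shoppers the figures are 0.29–0.30 (43–47%) and 0.48–0.50 (89–92%).

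**3. Sensitivity: trait also acts in explorers, at half the shopper slope, equal arm means.**
- Covariance = 0.436 × (2/3 + 1/6) = 0.364.
- Variance = 1 + 0.190 × (2/3 + 1/12) = 1.143.
- r = 0.364/√1.143 = 0.34; power at n=60 = Φ(0.354 × 7.55 − 1.96) = 76%, no worse than 73% in shoppers.

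Dilution therefore depends on the trait being nearly inert in explorers.

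**4. Precision of the slope difference.** Simulated power for a true shopper r against 0 in controls is about 18–20% at 0.30, 31–32% at 0.40 and 50% at 0.50. Approximately, SE = √(1/17 + 1/37) = 0.293, so the 95% half-width is 2.00 × 0.293 = 0.59, against a true difference of 0.44 at r=0.4.

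**The case against.** The strongest reply is that the article never says the arms are pooled. A reader might infer that all 60 enter one correlation, and that is the natural reading because condition is attached to the ANOVAs and not to the correlations. But the text names no analysis set, and an article may leave that to the full plan. So pooling cannot be charged as a stated choice. The misattribution point survives because it does not need pooling: a correlation in shoppers alone has the same flaw.

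A reader might also infer that pooling is what makes a headset trait look like a shopping trait. The figures in step 1 do not support that. The cause is the missing contrast; only the dilution in step 2 comes from pooling.

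A third tempting inference is that the trait cannot act in the control arm. The protocol does not support it: explorers have no assigned task, but every shopping action is enabled and they may fill a cart. A zero slope there is an assumption, as step 3 shows. Nor is a trait that acts in every arm irrelevant to shopping; it still affects fatigue while shopping, only not specifically.

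The aims can also be read as naming the setting and not an excess over exploration, and the sentence on susceptibility in the analysis section does not mention shopping. On that reading a single correlation is adequate, but then the results should be worded as fatigue in the VR session. The symptom questionnaire before and after immersion is a partial safeguard, but it is not linked to these correlations. Finally, the word primarily leaves some room for other methods, though none is named for the trait question.

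**Conclusion.** The concern holds in a limited form. As written, the trait analyses name correlation without condition and without a trait-by-condition contrast, so they cannot support the aim of identifying susceptibility specific to shopping. The control arm that could do so is not used for it.

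The misattribution result is robust across the assumed arm means: at r=0.4 a non-specific trait is usually significant, pooled or in shoppers only. The dilution result is conditional on two things the protocol does not state: that the control is pooled, and that the trait has little or no effect in explorers. Equal allocation of 20 per arm is also assumed. None of this affects the ANOVA comparisons of mean fatigue. This is a cheap improvement to an exploratory part of the plan.

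**What to change.** In Analysis, Phase 2, replace the single trait correlation by a model of VAS-F change on trait, condition (three levels) and trait × (experience 2 or 3 versus experience 1). Report for each trait the shopper slope, the control slope and their difference with a 95% CI, labelled exploratory. Say explicitly how experience 1 enters each trait analysis.

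Describe any single-slope association as fatigue in the VR session. Judge shopping specificity from the interval of the slope difference, not from a significance cut-off: with about 31% power at r=0.4 against 0, such a cut-off would miss a real difference about 69% of the time.

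The cost is one extra model term and a few lines of text, with no new data. The downside is a wide interval that will often leave specificity open, which is what 60 participants can show.

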### Immersive VR and Grocery Shopping

Virtual shopping environments have been used to evaluate how cognitive functions might operate in real-life situations [73-75] and may prove effective for the study of CF. Grocery shopping requires a combination of low and high levels of cognitive processes [8,73-75]. Looking for a specific product requires visual inspection, scanning, and focused attention. Traversing a shopping store requires visual attention (eg, looking for signs), spatial mapping, working memory, memory, and executive functioning [8,73-77]. Virtual shopping environments have been used successfully among individuals with significant cognitive impairment [8,78-81], and virtual shopping tasks correlate with real-life shopping activities [81,82].

We identified immersive VR grocery shopping as a suitable model to study fatigue associated with an IADL because it provides familiar but complex visual stimuli, affords the opportunity to search and choose, and presents the participant with well-known but complex cognitive challenges, such as comparisons, discernment, and decision-making. A potential disadvantage of using immersive VR to study CF is the risk of physical distress and eye strain in VR, which may confound the experience of CF or its measurement [83-85]. The risk of eye strain and other physical symptoms is reduced when high-quality head-mounted display (HMD) devices are used, motion is performed using physical walking or teleporting, the field of view is large, and each eye receives high-quality images [84]. In some cases, the realism of the environment must be sacrificed to reduce side effects.

We propose a 2-phase evaluation of the CF induction in VR. In phase 1, we will explore the feasibility of using immersive VR as a platform for studying CF using a user experience (UX) research methodology. We will use a combination of qualitative and quantitative approaches to identify components of the VR interface or environment that may contribute to feelings of eye strain or distress or make the shopping task difficult to perform. Phase 2 explores cognitive, environmental, and individual characteristics associated with VR-based grocery shopping–induced CF.

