For example, in phase 1, we will compare the participants’ self-reported physical symptoms and eye-related symptoms from the VRSQ before versus after completing the VR shopping experience. We will use the Wilcoxon signed-rank test, given the high probability of a nonnormal distribution in the dependent measure. This comparison will provide evidence to determine whether the VR environment produces physical distress or eyestrain. We computed the total scores for each of the observation scales. These totals inform about the number of times the participant had difficulties with the interface. We will compare the frequencies of interface problems in older and younger and male and female subjects using the chi-square test. These are structured statistical analyses planned as part of the formal UX results. Exploratory procedures are used to identify the relationship between user behavior (eg, number of items reviewed, distance traveled in the environment, and accuracy of shopping behaviors with measures of shopping enjoyment, shopping experience, and sense of immersion in the environment). For these analyses, we used Spearman rank-order correlations.

#### Phase 2

We will use the repeated measures analysis of variance (ANOVA) with the VAS-F and NASA-TLX as repeated dependent variables by shopping experience (fixed) to test the hypothesis that grocery shopping creates fatigue and workload, particularly when the person experiences interruptions and distractions. Secondary analyses will evaluate whether objective indicators of fatigue, such as eye tracking, shopping performance, and cognitive functioning (eg, pre- and postshopping processing speed and working memory) significantly differ by shopping experience using repeated measures ANOVA. A third series of analyses evaluated the relationship among individual characteristics, perceived CF, and workload. We will primarily use correlation to evaluate the relationship among pre-existing symptoms of fatigue, anxiety depression, personality traits, and fatigue susceptibility. Cognitive measures from the NIH toolbox will be correlated with perceived fatigue and workload to identify whether cognitive abilities influence the perception of cognitive workload and fatigue.

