The primary weakness of the study is the potential for the immersive VR environment itself to create feelings of eye strain and fatigue. This visual effect of the VR environment may have a stronger impact compared with the fatigue effects of the cognitive task, reducing the observed differences between experiences. We are mitigating the potential of VR-induced fatigue by using high-resolution HMDs. In addition, we will measure symptoms of physical distress pre- and postimmersion to identify any signs of physical distress that could affect the levels of self-reported fatigue. We are limiting the potential for motion sickness by using the teleport function for movement and other changes to the visual presentation to minimize any potential for headaches. The UX study is performed to specifically address questions of usability, including identifying any factors that might produce physical discomfort.

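### The phase 2 correlation of percent eye closure with self-reported fatigue, as described, takes no account of VR eye strain, although the VRSQ is collected and could show how much of the association strain explains

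*Protocol article*

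**What the plan says.** The Objectives section gives phase 2 a secondary aim "to identify performance and eye-tracking measures that objectively identify fatigue". Among its exploratory hypotheses is that "percent eye closure and gaze shift increase with time on task and are associated with self-reported fatigue".

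The phase 2 part of the Analysis section says how this will be examined: "Eye tracking such as percent eye closure will be explored as a possible objective indicator of fatigue". The first route is "by serving as a dependent measure in the repeated measures ANOVA by shopping experience"; the second is "in correlational analysis with self-reported fatigue and workload". No covariate is named for either.

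The article discusses eye strain in several places:

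- The Introduction section on immersive VR and grocery shopping refers to the "risk of physical distress and eye strain in VR, which may confound the experience of CF or its measurement".
- Strengths and Limitations treats eye strain and fatigue from the VR environment as the study's main weakness. It says symptoms will be measured before and after immersion to "identify any signs of physical distress that could affect the levels of self-reported fatigue".
- Study Design gives the VRSQ before and after VR in both phases, to help tell the effect of immersion apart from fatigue due to the shopping task. Table 1 confirms the VRSQ for phase 2.
- The only VRSQ analysis described is in phase 1: a before-versus-after Wilcoxon signed-rank test of "self-reported physical symptoms and eye-related symptoms from the VRSQ".

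**The concern.** Percent eye closure is derived from eye openness recorded inside the headset. If the headset or the visual work strains the eyes, a participant with more strain might close the eyes more and also rate fatigue higher. The two measures would then correlate across participants even if eye closure carried no information about cognitive fatigue.

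Randomization does not remove this. It balances people between arms, but the correlation is computed across people, and people differ in strain within each arm.

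At stake is how a secondary result is read. A positive correlation could mean that eye closure reflects cognitive fatigue, or that both measures reflect eye strain. The phase 2 data include the score that could help tell these apart, but the described analysis does not bring it in. The limitations text links symptoms to self-reported fatigue only and does not consider the eye measure.

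**Working it through.** The article states no figure on this point, so there is nothing to reproduce. The check has two parts.

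**1. What each planned route controls**

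| Source of eye strain | ANOVA by randomized arm | Correlation across participants |
|---|---|---|
| Common to all headset exposure | Balanced, because the exploration arm also spends 30 minutes in VR | Person-to-person differences remain |
| Differs by task (list-driven search versus free exploration) | Not balanced | Not removed |
| Used through the VRSQ in phase 2 | Not described | Not described |

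**2. How far a shared cause could carry the correlation**

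Inputs: n = 60 (Participants section). Everything else is assumed: two-sided alpha 0.05, strain S loading equally (a) on percent eye closure P and on self-reported fatigue F, no direct link between P and F, and a strain score of reliability ρ.

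Expected plain correlation: r = a × a.
- a = 0.3: 0.3 × 0.3 = 0.09
- a = 0.4: 0.4 × 0.4 = 0.16
- a = 0.5: 0.5 × 0.5 = 0.25
- a = 0.7: 0.7 × 0.7 = 0.49

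Critical value: r = t / √(n − 2 + t²), with t on 58 degrees of freedom. This gives 0.254 at n = 60.

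Partial correlation given score V: (r_PF − r_PV × r_FV) / √[(1 − r_PV²)(1 − r_FV²)]. Here r_PV = r_FV = a√ρ, so the expected value is a²(1 − ρ) / (1 − a²ρ).
- ρ = 1: 0 for every a
- a = 0.5, ρ = 0.8: 0.25 × 0.2 / (1 − 0.20) = 0.0625
- a = 0.5, ρ = 0.6: 0.25 × 0.4 / (1 − 0.15) = 0.118

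Share of simulated trials significant (20,000 replicates per setting):

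| Loading a | Plain r | Partial, ρ = 1 | Partial, ρ = 0.8 | Partial, ρ = 0.6 |
|---|---|---|---|---|
| 0.3 | 10–11% | 5% | 5% | 6% |
| 0.5 | 49–50% | 5% | 8% | 14% |
| 0.7 | 98% | 5% | 23% | 57% |

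A separate run of 10,000 trials at a = 0.4 gave 22% for the plain correlation and about 5% for the partial. With a = 0 both tests reject in 4.9% of trials, as they should.

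The simulated mean partial correlations at a = 0.5 (0.061 and 0.116) agree with the formula. Shopping arm was not part of the simulation.

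**The case against.** **The stated aim is modest.** A reader might infer that the plan validates eye closure by this correlation alone, so that a positive result could never be separated from eye strain. The text does not support that. It speaks of exploring a possible indicator, lists the hypothesis as exploratory, and attaches no decision rule. It also has the randomized ANOVA. A difference in eye closure between arms would not be explained by headset exposure alone, although strain that differs by task could still contribute. This objection stands.

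**The authors have not ignored eye strain.** They measure it, include a no-task VR arm, and use phase 1 to look for discomfort and revise the interface or exposure length. This also stands. What is missing is only the link from the VRSQ to the phase 2 correlation.

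**Covariates may be in a fuller plan.** The article never calls the correlation unadjusted, and a condensed article can leave such detail out. Fair, so the point concerns the analysis as described. Still, the article names this correlation and its variables and gives the VRSQ a purpose that no described phase 2 analysis serves. If the full plan already adjusts, nothing more is needed.

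**The causal premise is unproven.** No section says strain raises eye closure; the article says only that strain may confound fatigue or its measurement. The simulation shows what would follow from the premise and is no evidence for it. This stands.

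**Adjustment can remove real signal.** The Introduction names close visual work as a source of fatigue, so strain may lie on the path from task to fatigue. A noisy strain score also corrects only partly. Both stand, and they argue against making the adjusted result a strict test.

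**Conclusion.** The concern holds in a limited form. The between-person correlation as described cannot show whether an association between eye closure and fatigue is explained by VR eye strain, and randomization does not repair that. The article names the confounder and collects a measure of it in phase 2, but describes no phase 2 analysis that uses it.

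The size depends on assumptions the documents cannot settle. With equal loadings of 0.3 to 0.5, no direct link and n = 60, the plain correlation is significant in about 10% to 49% of trials, against a nominal 5%. At the low end the excess is small.

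This affects the interpretation of one exploratory secondary analysis. It does not touch the primary comparison of self-reported fatigue, and it does not make the eye-tracking aim unachievable.

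**What to change.** In the phase 2 analysis text, report the correlations of percent eye closure with VAS-F and with workload in two forms: unadjusted, and as partial correlations adjusted for the pre-to-post change in VRSQ eye-related symptoms and for shopping arm. Label the adjusted form a sensitivity analysis.

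Interpret the two together with the between-arm ANOVA. Describe an association that largely disappears on adjustment as not distinguishable from eye strain. Do not make the adjusted result a pass/fail rule.

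The cost is a few more lines of output from data already collected. There are two downsides to state alongside the result:

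- Adjustment is conservative if strain partly results from the task or from fatigue. Adjusting for arm likewise removes any association that arises because arms differ on both measures, which the ANOVA shows separately.
- Adjustment is incomplete if the VRSQ eye score is noisy, so an association that survives it does not by itself rule out strain.
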